## 5 Monitoring and Evaluation Methods

Table 7 presents the data collection methods used for evaluation of the performance metrics previously outlined in Table 3, and the target population. Estimating intervention treatment coverage will be assessed through the midline cross-sectional household survey. The impact of interventions on nutrition health outcomes will be assessed through the three repeated cross-sectional household surveys. The impact of interventions on malaria health outcomes will be assessed through a case-control study using a malaria tracker where cases will be recruited from health facilities and control from the midline household survey. Cases will be recruited from facilities due to the challenge of identifying sufficient numbers of acute malaria episodes via monthly household surveys. Focus Group Discussions (FGDs) will be used to provide context to the results. CHAI will contract a private data collection firm to carry out the household surveys, case control study, collection of health facility records, and completion of FGDs. CHAI will carry out the data analysis and provide CIFF the full clean datasets from the firm upon request to validate findings.

Table 7: The data collection methods used for evaluation of the performance metrics previously outlined in Table 3, and the target population.

| Data Collection Method                                              | Timeline      | Inclusion Age*                | Location                     | Indicators                         |
|---------------------------------------------------------------------|---------------|-------------------------------|------------------------------|------------------------------------|
| Baseline Household Survey                                           | July 2014     | 6-24 months                   | Community                    | Malnutrition                       |
| Midline Household Survey
Nutrition Module
SMC Coverage Module | November 2014 | 6-28 months
(3-63 months)^ | Community                    | Malnutrition
Treatment Coverage |
| Endline Household Survey                                            | May 2015      | 12-34 months                  | Community                    | Malnutrition
Prevalence         |
| Malaria Case Tracker                                                | Continuous    | 6-24 months in July 2014      | Health Facility
Community | Malaria Incidence                  |

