### **Malaria Case Tracker**

In order to assess the relationship between the treatments and malaria health outcomes, a case-control study will be used. The study population includes any child between the ages 6-24 months in July 2014 residing in the interventions areas. The study will begin following the first round of administration, and will continue until adequate numbers of cases and controls have been recruited (with a maximum of two months following the final round of distribution even though the estimated sample size may not be reached). The outcome of interest is confirmed clinical malaria (including severe cases) with cases defined as any child from the study population with a positive malaria test by either a Rapid Diagnostic Test (RDT) or microscopy. Controls are defined as children whose caregivers report they meet the following two inclusion criteria: 1.) no previous malaria symptoms (no fever in the last 4-weeks) and 2.) no care was sought for fever or other malaria symptoms in any health facilities since beginning of July 2014) will be recruited as controls. The assessed exposure is whether the children received SMC, SMC and nutrition products, or neither.

Starting directly after the first administration period, cases and controls will be recruited from health facilities. Information from both cases and controls will be collected through a short (about 30 minutes), pre-tested, malaria-case tracker that covers demographics (age, gender, ward of residence), malaria symptoms and severity, and nutrition indicators, and intervention exposure status (whether the child received SMC or nutrition products). Health care workers will be trained on case eligibility criteria and will collect the data on the child from the parent/guardian. Health care workers will be given a job aid that will assist them in classifying severe versus uncomplicated malaria based on the child's symptoms using the Nigerian National Policy. Data from the tracker will be aggregated by a trained health care

worker on a weekly basis and collected by CHAI staff through routine visits. Small facilitations fees will be given to health facilities for participation.

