Assuming intervention coverage in the population of ~60% and a detectable odds-ratio of 0.6 (odds of receiving SMC + LNS among malaria cases compared to SMC alone), we would need to recruit 326 cases (aged 6 to 24 months) with a power of 90% and alpha of 5%. To increase power, controls will be selected at a ratio of 4 controls:1 case, meaning we will select 1,304 controls. Assuming approximately on average 5-6 confirmed cases of malaria, per health facility per month, recruitment will occur in 10 health facilities over a 6 months period August 2014-January 2015.

Case-control inclusion criteria are that the child must:

- 1.) Reside in the intervention catchment area
- 2.) Be 6-24 months of age at the start of the intervention (July 2014)
- 3.) Have a parent/guardian that provided informed consent (for parents/guardians who are between the ages of 12-18 they must provide informed assent and if their parent/guardian is nearby, this parent/guardian must also provide informed consent form)
- 4.) Must be eligible for SMC/LNS delivery (see eligibility criteria on pages 11-14)
- 5.) Cases must be parasitologically confirmed by either RDT or microscopy
- 6.) Controls must have had no previous malaria symptoms (no fever in the last 4-weeks) and no care was sought for fever or other malaria symptoms in any health facilities for them since beginning of July 2014)

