### **Potential Benefits to Participants**

Children who receive SP-AQ will be at significantly lower risk for malaria transmission and the associated risks of malaria. Households that participate in the SP-AQ administration will be at lower risk for the economic loss associated with malaria sickness within the household. Children who receive LNS will be at significantly lower risk for malnutrition and the associated risks of being immuno-compromised as a result of malnutrition. Households that participate in the SP-AQ +LNS administration will be at lower risk for the economic loss associated with sickness within the household. All CDDs and health facilities recruiting cases for the case control study will receive a small facilitation fee for their contributions to the study.

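### Controls, but not cases, are screened on fever and fever care since July, so an LNS effect on non-malarial febrile illness could appear as malaria protection

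*Protocol*

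**What the plan says.** The Malaria Case Tracker subsection of section 5 gives the two definitions.

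- **Cases:** "cases defined as any child from the study population with a positive malaria test by either a Rapid Diagnostic Test (RDT) or microscopy". The criteria list repeats this: "Cases must be parasitologically confirmed by either RDT or microscopy". The shared criteria (residence, age, consent, SMC/LNS eligibility) also apply. Nothing restricts a case's earlier fevers or facility visits.
- **Controls:** "Controls are defined as children whose caregivers report they meet the following two inclusion criteria". The two criteria are no fever in the last 4 weeks and, in the words of criterion 6, "no care was sought for fever or other malaria symptoms in any health facilities for them since beginning of July 2014". No malaria test is stated for controls.

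The exposure is receipt of SMC, of SMC with nutrition products, or of neither. The sample size is framed on SMC+LNS versus SMC. The first round begins on July 15 (SP-AQ Dosing Procedures), so nearly all of the look-back falls after treatment starts.

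The source of controls is stated in two ways. The opening of section 5 says "cases will be recruited from health facilities and control from the midline household survey", whereas the Malaria Case Tracker subsection places recruitment of both groups in health facilities.

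**The concern.** Controls should show how common the exposure is among the children who would have become cases. This rule removes from the controls every child taken to a facility with fever or malaria-like symptoms from any cause over several months, and puts no matching restriction on cases. Whether a child passes is partly a post-treatment outcome. If LNS reduces non-malarial febrile illness, SMC+LNS children pass more often, exposure among controls rises, and the odds ratio falls below 1 without any change in malaria. This is the contrast on which the study is sized, and clinical malaria is one of its three primary outcomes.

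Care-seeking is a second route. Cases are by design children brought to a facility, while the rule favours controls who were not. This distorts the odds ratio wherever care-seeking is related to exposure.

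**Working it through.** **The plan's figure.** With 60% exposure in controls and an odds ratio of 0.6, exposure in cases is 0.6×0.6/(1 + 0.6×(0.6 − 1)) = 0.36/0.76 = 0.474. Comparing 0.474 with 0.60 at two-sided 5%, 90% power, 1:1, pooled variance and no continuity correction gives 326 cases, as stated. With 1,304 controls the power is about 98%. The concern does not alter these numbers, but high precision makes a modest artefact easier to declare significant.

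**LNS contrast, true malaria odds ratio 1.** Every input here is an assumption:

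- s = share of children taken to a facility when febrile
- f = chance of a non-malarial fever from July to the control interview
- RR = LNS effect on that fever
- m = malaria chance, 0.15 in both arms

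The chance of passing the care rule is E(f) = (1 − s) + s(1 − m)(1 − f), with f×RR replacing f under LNS. The apparent odds ratio is E(f)/E(f×RR). For s = 0.8, f = 0.6, RR = 0.8: E = 0.2 + 0.68×0.40 = 0.472 and 0.2 + 0.68×0.52 = 0.554, so the ratio is 0.85.

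| s | f | RR | Apparent OR | Chance of a falsely significant protective result |
|---|---|---|---|---|
| 0.5 | 0.2 | 0.9 | 0.99 | 3% |
| 0.5 | 0.4 | 0.8 | 0.96 | 5% |
| 0.8 | 0.4 | 0.8 | 0.92 | 10% |
| 0.8 | 0.6 | 0.8 | 0.85 | 24% |
| 0.8 | 0.6 | 0.7 | 0.79 | 44% |

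The last column uses 326 cases, 1,304 controls and 60% exposure in cases; its nominal value is 2.5%. Excluding only malaria, and not fever care, returns 1.00 in every row. The 4-week fever rule is not modelled; it acts in the same direction.

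**A simpler formula overstates the shift.** Let v be the share of SMC-only children with any fever visit and r the LNS cut in visits. Then (1 − v)/(1 − v(1 − r)) with r = 0.2 gives 0.83 at v = 0.5 and 0.68 at v = 0.7. This applies the cut to malaria visits too, which contradicts the assumption of no malaria effect. Now suppose 30% have a malaria visit, independent of other fever, and only non-malarial fever is cut by 20%:

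- v = 0.5: non-malarial visit risk is 1 − 0.5/0.7 = 0.286, cut to 0.229. OR = 0.50/(0.7×0.771) = 0.93.
- v = 0.7: the risk is 1 − 0.3/0.7 = 0.571, cut to 0.457. OR = 0.30/(0.7×0.543) = 0.79.

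**Enrichment, if controls come from the community.** The share of non-care-seekers among controls is (1 − s)/E(f). In the rows above it rises from 50% of the population to 60–66% of controls (s = 0.5), or from 20% to 33–42% (s = 0.8). Among cases it is 0% by construction.

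**SMC contrast, no true effect (assumed example).** Half the families seek care for 80% of fevers and half for 20%; 70% of children are febrile; SMC uptake is 70% and 50% respectively.

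- Cases' exposure: 0.8×0.7 + 0.2×0.5 = 0.66.
- Controls with the rule: pass rates are 1 − 0.7×0.8 = 0.44 and 1 − 0.7×0.2 = 0.86, so exposure is (0.44×0.7 + 0.86×0.5)/1.30 = 0.568.
- Controls without the rule: 0.60.
- Odds ratios: (0.66/0.34)/(0.568/0.432) = 1.48 with the rule, and (0.66/0.34)/(0.60/0.40) = 1.29 without it.

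The rule multiplies the odds ratio by 1.48/1.29, about 1.14. The larger part comes from finding cases at facilities.

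**The case against.** The rule has a purpose. Control status rests on caregiver report, and with no test stated the fever and care history is the only screen against malaria among controls. That stands as a reason for some screen at recruitment. It does not justify excluding fever visits of any cause over months in one group only.

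The size is unknown. The documents give no fever rate, visit rate or LNS effect, and the mildest scenarios are harmless. This stands in full.

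Table 3 also measures malaria as incidence per 1,000 in facility catchments, which uses no controls, so H-3 does not rest on the odds ratio alone. The care-seeking example varies uptake between families, whereas the powered contrast compares arms assigned by area. The two biases can also run in opposite directions. These points limit the severity, but cancellation cannot be relied on.

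Some stronger readings are tempting but unsupported:

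- A reader might infer that any LNS effect on other illness would look like malaria protection. Only recent fever, or febrile or malaria-like illness taken to a facility, acts through the rule.
- A reader might take the benefits section to predict fewer fever visits. It says "Children who receive LNS will be at significantly lower risk for malnutrition and the associated risks of being immuno-compromised", which makes an effect plausible but mentions neither fever nor visits.
- A reader might conclude that non-care-seekers fill the control group. They are enriched, since healthy children of care-seeking families still qualify. If controls are recruited at facilities, even the enrichment weakens.
- A look-back that lengthens during recruitment follows only if controls are recruited continuously, not at the midline survey alone.

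Adjustment for care-seeking could be specified in an analysis plan not seen here. The eligibility rule is fixed in the protocol, however, and adjustment cannot restore excluded controls.

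**Conclusion.** The asymmetry is explicit and stated twice, and it makes control eligibility depend on a largely post-treatment outcome. Under a true null for malaria, the SMC+LNS versus SMC odds ratio would lie at about 0.79 to 0.99 over the assumed inputs if LNS lowers non-malarial febrile illness. At the extreme, 0.79 is ln 0.794/ln 0.6 = 0.231/0.511, about 45% of the log effect the study is sized to detect; at the mild end the shift is negligible. If LNS raised such illness, the error would run the other way.

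The LNS mechanism holds wherever controls are found. The care-seeking mechanism applies mainly if they come from the household survey. It needs care-seeking to differ by exposure, and it adds to a bias that facility-based case finding already creates (1.29 to 1.48 in the example). The rule should be fixed, but the documents do not show that the malaria result would be invalid without the change.

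**What to change.** 1. Delete the since-July care clause from both places in the Malaria Case Tracker subsection.
2. Define a control as an eligible study-area child without current fever who is not currently a malaria case, by caregiver report or existing facility record, at the recruitment or interview date. This requires no new testing. If a look-back is kept, make it short and apply the same one to cases (before the present episode) and controls.
3. Add tracker questions on usual care-seeking before round 1 for both groups, and adjust for it.
4. Reconcile the opening of section 5 with the Malaria Case Tracker subsection on where controls are recruited.

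The cost is revised wording, a fixed reference date for controls and a few questions; more children qualify as controls. Some controls will have had an earlier or undetected malaria episode. Earlier episodes are acceptable when controls represent children at risk when cases arise. Undetected current infection would pull the odds ratio slightly toward 1. The change must precede control recruitment, because excluded children cannot be recovered afterwards.

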### **Focus Group Discussions**

In order to identify the barriers and facilitators to SMC and LNS delivery and provide context to the study, 6 FGDs will be completed. FGDs will occur among parents/guardians and CDDs, three FGDs in each intervention area (2 per arm with caregivers and 1 with distributors). Ward officials will be asked to recruit participants. Ward officials will be asked to select a mix of individuals who represent a diverse range of knowledge, attitudes, and practices and would be willing to participate. It is expected that focus group discussions will take between 45-60 minutes and light refreshments will be provided afterwards. Questions will be targeted at strengthening CHAI's understanding of perceptions, challenges, and provide ideas for providing recommendations for co-packaging SMC + nutrition interventions and will occur in Hausa. The FGDs could also provide context to the malnutrition indicators and intra-household nutrition equity and distribution. Every participant must be over the age of 18 and have provided informed consent prior to participation.

### **Monitoring Data Collection Procedures and Participant Recruitment**

The following 5 programmatic data forms will be created and used in this study.

#### **Stock Logbooks**

Each CDD will be provided a stock log at training and will be instructed on how to fill in the stock register. As part of their involvement in this study, they will be requested to ensure a daily stock log is completed tracking daily availability of SP-AQ. If they do not feel able to complete the stock logs, they

will not be able to participate in administration. It is expected to take less than 5 minutes per day to fill out the register. Study staff will return after each administration round to collect data. The purpose of the stock logs is to provide on-going data on the number of treatments administered and remaining with CDDs in each treatment area.

### **Treatment Registers**

Each CDD will be provided a treatment register at training and will be instructed on how to fill in the register. Every child that receives a dose of SP-AQ or SP-AQ + LNS will need to be entered into the treatment register before administration. As part of their involvement in this study, they will be requested to record the name, age, sex, and contact details of each child that they administer treatment to. If they do not feel able to complete the treatment register, they will not be able to participate in administration. It is expected to take less than 1 minute per patient to fill out the register. Study staff will collect the books after administration round 4. The purpose of the treatment registers is to provide on-going data on the number of treatments administered and to whom in each intervention area and assist with the development of the sampling frame for the control portion of the case-control study.

### **Treatment Cards**

Every child 3-59 months in July 2014 reached by a CDD will be assigned an ID and their parent/guardian will be given a treatment card. Each time a child receives a treatment their parent/guardian will be asked to provide their treatment card and the CDD will record the dose and date of administration on the child's card as a record of the child's participation in the study. If the child is ineligible for treatment, the CDD will also record this on treatment card. The parent will be asked to keep the card in a safe place. The purpose of the treatment card is to provide a record of what treatment was provided, to which child, and the date of administration. It is both a record for the parent and will be also be referred to during the household survey.

### **Referral Forms**

During any round of administration or data collection activity, any child found to be severely malnourished will be recorded on the nutrition referral form and immediately be referred to the nearest CNAM for treatment.

### **Drug-Adverse Reactions Form**

For any child that experiences a severe reaction to either SMC or LNS a Drug Adverse Reactions Form (ARF) will be completed and the child will be referred to the nearest public health facility for further observation or treatment. Additional details are included in the *Potential Risks to Participants* section on pages 19-20.

## **6 Ethical Considerations**

This study will be submitted to the Research and Ethics Committee of Kano State Ministry of Health, under the Hospitals Management Board, for approval. Further clearance to conduct the study will be sought from the KSMOH through the KSMCP and from the District Health Officers (DHOs) in the selected

wards. Informed consent will be collected from all participants enrolled in the study prior to their inclusion.

### Potential Risks to Participants

While SP+AQ is safe and well tolerated when used in recommended doses and regimens mild side effects may occur of which the most common is vomiting associated with AQ ingestion. Severe side effects including severe skin reactions and blood dyscrasias are rare. In Senegal nearly 800,000 treatment courses of SMC with SP+AQ were given to children; no serious adverse events attributable to SMC drugs were detected despite a high level of surveillance. To mitigate side effects, children will receive SP-AQ with purified water and parents/guardians will be instructed to have fed the child prior to drug administration. Each child will be observed for 15 minutes post-ingestion for signs of dangerous side effects. Drug administrators will be trained and well versed on the signs of danger to watch for; the consent form will also outline this to the child's parent/guardian. At the first sign of a life-threatening adverse reaction the child will be immediately referred to the nearest health center. Emphasis will be given to the voluntary nature of participation in the consent form and during the study. Participants will be informed that they are free to discontinue participation at anytime and that whether or not they participate will not affect their ability to get treatment in health facilities or access other services within the community in the future.

Similarly, with Plumpy'Doz™, while unlikely, there is a small chance of a child having an allergic reaction to the peanut component of the product. The allergy may cause reactions in the form of: skin changes (hives, rashes and infections); body swelling; shortness of breath; and anaphylactic shock. To monitor potential side effects during the first ingestion of Plumpy'Doz™ each child will be observed for 15 minutes post-ingestion for signs of dangerous side effects. Drug administrators will be trained and well versed on the signs of danger to watch for; the consent form will also outline this to the child's parent/guardian. At the first sign of an allergic reaction or a life-threatening adverse reaction the child will be immediately referred to the nearest health center. Emphasis will be given to the voluntary nature of participation in the consent form and during the study. Participants will be informed that they are free to discontinue participation at anytime and that whether or not they participate will not affect their ability to get treatment in health facilities or access other services within the community in the future.

In addition to routine monitoring, as part of routine surveillance, any child who experiences adverse reactions will be recorded on a drug adverse reaction form. For severe drug adverse reactions, the child will also be referred to the nearest public health facility. All local health facilities as well as CDDs will be briefed on the reporting procedure.

Table 5: Reporting Procedure for Severe Adverse Reaction.

|        |                                                                                                                                                              |
|--------|--------------------------------------------------------------------------------------------------------------------------------------------------------------|
| Step 1 | TREATMENT (Discontinue drug and manage symptoms, e.g. through use of systemic corticosteroids such as hydrocortisone to accelerate recovery in severe cases) |
|--------|--------------------------------------------------------------------------------------------------------------------------------------------------------------|

|        |                                                                                 |
|--------|---------------------------------------------------------------------------------|
| Step 2 | Complete the Drug-Adverse Reactions Form (ARF)                                  |
| Step 3 | Immediately contact CHAI study staff using the phone number listed on the (ARF) |
| Step 4 | CHAI study staff will record the event and alert NAFDAC                         |

The greatest risk to participants that participate in the FGDs, interviews, or fill in registers and stock logs are the time required. The participants will be asked where they wish to take the survey, which will help to ensure that they are comfortable and that their privacy is maintained. All data collection activities will be kept as brief as possible and will only be collected from those that have provided informed consent. Participation in any data collection activity will be voluntary.

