### **Phase 2: Intervention Administration**

Phase 2 will make use of the existing network of Community Drug Dispensers (CDDs) that work on other health campaigns in Kano. Community lists will be obtained for each ward from the Village head or the CDD LGA Focal person. Within each ward, CHAI study staff will visit each identified community and a household sampling frame will be obtained from each community headman. In the event that a Village head cannot produce an accurate listing or new communities have developed that are not present on the village head's list, the village headman and CDDs will be used to create a census of their community. CDDs alongside study staff will visit each household on the sampling frame and obtain accurate listings of homes with at least one child under-five residing within it in the treatment area. Supplementary data will also be collected from parents/guardians including data on the number of children 3-59 months of age residing in each home, child and parent's/guardian's names, and contact details (e.g. phone number of parent/guardian, address of home).

CHAI will train pre-existing CDDs on the proper administration of SP-AQ/*Plumpy doz'* in a 1-day training course. During each administration period, each CDD will be assigned to 100 households that they will cover over the course of one week. The CDDs will visit children and their parents/guardians in their homes four times on a monthly basis (July-October) and deliver the treatment. After each visit, CDDs will instruct parents/guardians that they will return four weeks later, on the *same day of the week* as the first SMC visit to deliver the next treatment.

All treatments provided will be recorded in two places: a treatment card that is left with the parent/guardian of the child and the CDDs administration register. Each child will be assigned a unique Identification number (ID) and the treatment card and the child's name in the CDDs administration register will be labeled with the unique ID. The treatment card will be filled out by the CDD at first contact, and given to the parent/guardian of each child. Information collected on the treatment card will include the child's name, birthday, dose of SP-AQ and amount of LNS provided, date of

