## **SP-AQ Administration**

### **Dosing Procedures**

The KSMOH and the KSMCP provided administration clearance for mass drug administration, dosing, and the study procedures. Dosing guidelines for SP-AQ are presented in Table 5 below and follow the WHO guidelines for SP-AQ delivery. SP-AQ will be provided once per month, ideally on the same day each month, for 4 consecutive months during the long rainy season (July 15 – October 15). A person trained in SP-AQ administration and the signs and symptoms of adverse reactions will administer the SP-AQ. Following drug ingestion, children will remain under observation for 15 minutes. In the event of spit-up or vomiting drugs will be re-administered alongside food, water, or breast milk. The first dose of SP-AQ, consisting of both SP and AQ tablets, will be administered through directly observed therapy (DOT) whereby children are observed taking the drug by the health worker or parent /guardian administering the drug. Parents/guardians will then be given the remainder of the co-blister (containing two AQ tablets each given on the respective two days) and instructions on how to administer the drug on days 2 and 3. In young children unable to swallow the SP-AQ, the CDD will recommend that the SP-AQ tablets be crushed and mixed with water and sugar. The CDD will provide sugar for the full three days of treatment.

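### Active observation for reactions ends 15 minutes after the visit dose, no later contact is stated to ask about them, and the protocol gives two thresholds for the adverse reaction form

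*Protocol*

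**What the plan says.** **Observation.** The SP-AQ Dosing Procedures state: "Following drug ingestion, children will remain under observation for 15 minutes". Section 6, Potential Risks to Participants, repeats this for SP-AQ: "Each child will be observed for 15 minutes post-ingestion for signs of dangerous side effects". For LNS the same section ties the watch to the first ingestion: "each child will be observed for 15 minutes post-ingestion for signs of dangerous side effects".

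**Doses at home.** Only the first dose of each three-day course is directly observed. Caregivers receive the remaining amodiaquine tablets and "instructions on how to administer the drug on days 2 and 3". LNS is then served daily at home.

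**Later contacts.** Phase 2 says: "The CDDs will visit children and their parents/guardians in their homes four times on a monthly basis (July-October) and deliver the treatment". The midline survey follows in November 2014.

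**Named risks.** "Severe side effects including severe skin reactions and blood dyscrasias are rare". Vomiting is named as the most common side effect.

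**Passive route.** Potential Risks provides for adverse reactions to be put on a form as part of routine surveillance. It has distributors and all local health facilities briefed on reporting, and the consent form tells caregivers the danger signs.

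**Recording threshold.** Section 5, Drug-Adverse Reactions Form: "For any child that experiences a severe reaction to either SMC or LNS a Drug Adverse Reactions Form (ARF) will be completed". Section 6, Potential Risks: "any child who experiences adverse reactions will be recorded on a drug adverse reaction form".

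**The concern.** How reactions are found decides what a low count means. If nobody is scheduled to ask about the weeks after a dose, few forms may mean few reactions or few reports, and the data cannot tell these apart. The two form rules add to this. A facility following one section would file a form for a mild event, and a facility following the other might not, so a total does not show what severity it covers.

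This matters beyond the trial. The Introduction says that delivering LNS through the SMC campaign has not been done before, and sections 2 and 8 direct the findings at the States eligible for SMC and at global policy. The safety reassurance in Potential Risks comes from a Senegal programme described as highly surveilled, which used SP-AQ. The present protocol schedules no comparable active follow-up. How events are ascertained belongs in a protocol and is not a detail normally left to an analysis plan.

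**Working it through.** The protocol gives no safety sample size or event rate to reproduce. The check is simple arithmetic on its schedule, followed by a comparison of sections.

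**1. Drug-days under observation.** Inputs: four monthly rounds (Phase 2), a three-day course (Table 5), and direct observation of the first day's dose only (Dosing Procedures).
- Total per child treated in every round: 4 × 3 = 12 drug-days.
- Observed: 4 × 1 = 4, or 33%.
- Given at home: 4 × 2 = 8, or 67%.

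**2. LNS servings under observation.** Inputs: Table 6 and the LNS paragraph in Potential Risks.
- Days per monthly ration: 690 g / 23 g per day = 30; over four months, 4 × 30 = 120 days.
- Servings: 3 × 120 = 360.
- Observed: 1 of 360 (0.3%) if only the first ingestion is watched, or at most 4 of 360 (1.1%) if this is repeated each round.

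**3. Share of the interval.** 15 / (28 × 24 × 60) = 15 / 40,320 = 0.04%. This shows scale only. Risk is not uniform over the 28 days, so it does not measure the reactions missed.

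**4. What later contacts are stated to collect.**

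| Contact | Stated content | Question on reactions since last dose |
|---|---|---|
| Rounds 2 to 4, treatment card | Name, birthday, dose and LNS amount, dates; reason if excluded | None stated |
| Rounds 2 to 4, register | The above items plus sex, guardian and address | None stated |
| Midline survey, November 2014 | Coverage, adherence, nutrition | None stated |
| Distributor visit after round 4 | No visit planned | Not applicable |

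**5. The two recording rules applied to the same event.**

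| Event | Drug-Adverse Reactions Form section | Potential Risks section |
|---|---|---|
| Severe skin reaction | Form | Form |
| Mild vomiting | Not called for | Form |

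The step-by-step reporting table in Potential Risks is headed for severe reactions only, so it does not settle the second row.

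**The case against.** The best case for the protocol has four parts.

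- **There is surveillance after the 15 minutes.** A reader might infer that reactions are looked for only in that window. The text does not support this: the passive route covers any later time, and severe reactions are passed to study staff and the national regulator. What stands is that no contact is scheduled to ask.
- **Later rounds have some screening.** The exclusion criteria include allergy to either drug, severe acute illness and, for LNS, peanut allergy. The card records why a child was not treated, so a reaction recognised as an allergy could appear there. This is not a reaction history, and it misses an event that resolved or was not seen as an allergy.
- **The two form rules can be read together.** The Drug-Adverse Reactions Form section does not say that the form is limited to severe reactions, and it refers to Potential Risks for details. That softens the conflict to an ambiguity, but field staff with one day of training should not have to work it out.
- **The forms themselves are not shown.** The register, questionnaire and reaction form may contain more than the protocol lists. The finding therefore concerns what is stated.

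A reader might also infer that reaction counts cannot be compared between arms. That does not follow. Both arms share the SP-AQ observation and the ambiguous threshold, no differential ascertainment is stated, and no between-arm safety comparison is planned; the primary outcomes are coverage, malnutrition and malaria. Bias would need the two thresholds to be applied differently by arm. The LNS arm does have an extra watch at first ingestion, and its referral trigger is worded differently from the SP-AQ one. That wording concerns referral rather than the form. It should be reconciled, and no view is taken here on which is right.

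**Conclusion.** The point holds in two parts. First, the only scheduled look for reactions is 15 minutes after the visit dose and at the first LNS ingestion. For a child treated in all four rounds, 8 of 12 drug-days and almost all of about 360 LNS servings fall outside it, with passive reporting thereafter. The severe skin and blood reactions that the protocol names are therefore not actively sought. Second, two sections set different thresholds for the same form. Counts would be incomplete and of unclear severity, and a low count would be weak evidence of safety.

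The conclusion assumes that the unseen forms hold no reaction question beyond what the protocol describes. It does not rest on any onset time. A reader might call the named reactions delayed, but the protocol gives no timing; the gap exists for any reaction that begins after the window or after a home dose. Nor can the protocol's under-five mortality of 217 per 1,000 be used to size the gap. It is background mortality and includes deaths at ages that are not treated.

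The primary outcomes are unaffected. This is a low-cost improvement that should be made.

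**What to change.** 1. At rounds 2, 3 and 4, have the distributor ask, before dosing, about any reaction, admission or death since the last visit, and enter the answer in the register, including when the answer is none.
2. Put the same question in the November midline survey for round 4. This reaches surveyed households only. A household is listed only if it has a child of the inclusion age, so one whose only such child has died would be missed.
3. Reconcile the Drug-Adverse Reactions Form section with Potential Risks, so that both state one recording threshold. Either choice works for counting if it is stated once and applied in both arms.
4. Report counts by arm and round over children treated in that round, as descriptive data without a test. Show solicited answers separately from spontaneous forms.

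The cost is one register column, one or two survey questions and a wording correction, with no new visits or staff. The downside is about a minute more per visit and more non-specific reports. No dose, referral or treatment rule changes.
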